#### **5. Study design**

This will be a 2-arm, multicenter randomised clinical trial where one group will be allocated to NET-EN use and the other to DMPA. The group allocated to NET-EN will be the treatment group and those allocated to DMPA will be the comparison group, as the majority of women

in the research settings use DMPA. The follow up period will be a minimum of 7 months, and pending funding up to 18 months.

### **5.1 Methods and study procedures :**

The study design, procedures, inclusion and exclusion criteria, randomization procedures, follow up and data management are outlined below.

Biological samples will be collected at baseline, 6 months and 6 months 7 days to measure differences between women allocated to NET-EN versus DMPA in biological parameters relevant to HIV acquisition risk. Sample size: 520 participants

### **5.2 Study sites**

The research sites include the East London, Mdantsane, public health clinics and hospitals (Frere and Cecilia Makiwane Hospitals), and the research site of MatCH Research Unit (MRU), University of the Witwatersrand, based in KwaZulu Natal, South Africa. These sites have been chosen as they have research and diagnostic capabilities, demonstrated by successful participation in the current ECHO study, and are research units affiliated to University of the Witwatersrand.

### **5.3 Study participants**

Women attending health services in the collaborating Department of Health participating services and the study sites who, after routine counselling on all the methods available (Injectables, OC, IUD, Implant), request and are assessed as suitable for injectable contraception and meet the eligibility criteria, will be eligible for participation. Specific services for recruitment will include women attending family planning clinics women, women accessing pregnancy termination services and the general public.

#### **5.3.1 Participant recruitment**

Women requesting injectable contraception will be informed by the study recruitment team about the study and if they are interested, advised to go for HIV test at a health facility as the site will require recent results before they are screened for eligibility. The aim is to pre-screen all participants to reduce screen failures who might be HIV positive. Women expressing an interest will sign consent for screening and be assessed for eligibility using a screening form. A urine pregnancy test will be performed if pregnancy has not been ruled out clinically. Women who meet the entry criteria will be fully counselled and informed in their preferred language (informed consent sheet attached) and invited to participate. Emphasis will be placed on HIV risk reduction including condom use. Women will be offered time to reflect and ask questions, and

to go home to consider or consult with family members if they wish to. Women who agree to participate will sign informed consent (form attached).

Exclusion of pregnancy and clinical assessment for STI's or contra-indications to family planning methods are part of the routine health services assessment for family planning and not specific to the research, and any illness or pregnancy detected will be managed in the routine service.

## **5.4 Eligibility Criteria**

### **5.4.1 Inclusion criteria**

- Requests injectable contraception and intends to continue contraception for at least 18 months.
- Aged 18 to 40 years. Legally competent to sign consent according to local regulations..
- Prepared to use either NET-EN or DMPA
- Prepared to accept follow-up procedures and able to fulfil these procedures, including routine HIV tests according to national guidelines (see below).
- After full counselling, decline to use PrEP
- Understands patient information form and signs informed consent.

### **5.4.2 Exclusion criteria**

- Received DMPA in previous 6 months or NET-EN in previous 4 months
- HIV positive
- Planning to move out of study area in next 18 months
- Participating in another clinical trial
- <6 weeks postpartum or post-abortion
- Does not meet MEC criteria or local national guidelines for NET-EN or DMPA use.
- Using or intending to use medication which may interfere with biological measurements, for example steroids or drugs affecting renal function such as PrEP. Prospective participants will be fully informed about PrEP, and if interested in using PrEP, will be referred to any available local providers. Participants who, after recruitment, change their minds and decide to access PrEP services, will be kept in the study.

## **5.5 Sampling and allocation**

The anticipated recruitment proportions will be 50% per site. Recruitment will continue at both sites until the total sample size is reached.

## 5.6 Sample size calculation

Primary psychological outcome: Depression

In our previous study, 24 MADRS scores in women randomized to NET-EN were 8.3 (standard deviation 7.5). Based on this standard deviation, to show a difference of 2 between the study groups with 95% certainty and 80% power would require 221 participants per group, and allowing for 15% loss to follow-up, 260 per group. (<http://pharmaschool.co/size4.asp>).

Primary biological outcome: serum 17 $\beta$  estradiol

In our previous study, 17 $\beta$  estradiol levels in women randomized to NET-EN were 136 pmol/L (standard deviation 119). Based on this standard deviation, to show a difference of 35 pmol/L in either direction between groups with 95% certainty and 80% power would require 181 participants per group, and allowing for 15% loss to follow-up, 213 per group (<http://pharmaschool.co/size4.asp>).

Because of multiple outcomes to be measured, the remaining outcome comparisons will be regarded as exploratory. In general, studies of biomarkers such as immune effects have used considerably smaller sample sizes.

### *Feasibility of recruiting necessary sample size*

Effective Care Research Unit has access to 18 primary health care centers where recruitment will take place. MatCH Research Unit has access to a large family planning clinic in Ethekwini, Kwazulu Natal.

We estimate recruitment for the 2 sites should be at least 40 per week, with completion in 12 weeks.

## 5.7 Description of the intervention

The administration of NET-EN or DMPA injections will be performed by an appropriately trained health professional members of the research team. If for logistical reasons an injection is given by routine health service staff, it will be documented by research staff. Clinical procedures will follow local practice guidelines. The allocated injectable method will be provided and followed up in the study site. All participants would be receiving one or other injectable method in the routine service if they were not in the trial. Both injectable methods are available in the health services, and they will be referred to the routine system for their on-going family planning care after the conclusion of the trial.

### 5.7.1 Drugs and devices

3. Norethisterone enanthate 200mg intramuscular (NET-EN)

4. Depot medroxyprogesterone acetate 150mg intramuscular (DMPA IM)

## **5.7.2 Administration of study products**

### *DMPA administration*

For women randomised to DMPA, research staff will inject the initial IM injection of DMPA (medroxyprogesterone acetate sterile aqueous suspension 150 mg per 1 mL) at enrolment. Subsequent injections will be given every 3 months at the study site.

Sites will assess participants who are more than 4 weeks late for their DMPA injections for pregnancy prior to administering a subsequent injection.

### *NET-EN administration*

This study will use Nur-Isterat®, manufactured by Bayer HealthCare. Women randomised to NET-EN will receive the initial injection of 200 mg IM at enrolment. Subsequent injections will be given at 2-month intervals. Sites will assess participants who are more than 2 weeks late for their NET-EN injections for pregnancy prior to administering a subsequent injection.

The 2-, 4-, 8-, 10-, 14- and 16-; or 3-, 9, and 15-month visits will be contraception-only visits. Months 6, Month 6,7days, and pending funding 12 and 18 will be the study visits.

## **5.8 Study procedures**

### **5.8.1 Recruitment and screening**

All potentially eligible women who after routine family planning counselling have chosen an injectable progestogen, will be offered HIV testing (and CD4 counts if indicated) as part of their routine care in the health service, and using routine health service methods. HIV positive women who do not currently have routine HIV care will be referred to care within the routine health service. Women who test HIV negative will be asked if interested in participating in the trial, and assessed for inclusion.

All women being considered for recruitment will be screened for eligibility (see section 5.4). Those who are ineligible or choose not to participate will regardless be offered the contraception of their choice, according to the government family planning policy.

### **5.8.2 Enrolment procedures**

Baseline details will be recorded from participants (see attached data collection sheet). All study procedures will be carried out in premises with appropriate privacy :

- Baseline demographic, psychological, physiological and behavioural data will be recorded
- Baseline blood (40ml venous blood) and genital tract samples (cytobrush and vaginal wall swabs) for immunological and hormonal studies, and dried blood spots for HIV PCR will be collected.
- Participants will be counselled on all HIV prevention strategies (including condom use and pre-exposure prophylaxis, and their availability in the public sector).

**Table 1: Screening and Enrolment activities**

| Activities                                                      | Staff                 |
|-----------------------------------------------------------------|-----------------------|
| Notice information +IC – [15-30min]
Locator information      | Counselor             |
| Eligibility assessment (CRF1 Scr) - [15min]
Demographic data | Study Nurse           |
| HIV counselling and test – [30min]                              | Counselor             |
| Clinical interview (CRF2) - [30min]                             | Clinician/Study Nurse |

|                                                             |                       |
|-------------------------------------------------------------|-----------------------|
| Clinical assessment (CRF3) - [30-40min]                     | Clinician/Study Nurse |
| Anthropometric measures (height,weight)
(CRF3) - [10min] | Clinician/Study Nurse |
| BDI-II & ASEX - [15min]                                     | Counselor             |
| Blood and genital tract sample collection* -
[30min]     | Study nurse           |
| Randomisation                                               | Study nurse           |

### 5.8.3 Randomization procedure

Allocation lists will be prepared by SA Medical Research Council (MRC) using computer-generated random sequence in balanced blocks of variable size, stratified by study site. Women who agree to participate will be entered onto a trial register and then randomized by accessing an online randomization service hosted by SA MRC. In the event of difficulty accessing the online service, a separate series of randomized allocations will be available in sequentially numbered, sealed opaque envelopes, or by telephone back-up service. Every effort will be made to use the back-up system only when essential. The point of trial entry will be the online group allocation or opening of the envelope.

### 5.8.4 Follow-up visits

All participants will be asked to attend the research sites at the time of their repeat injections (2- or 3-monthly). At the 6-month and month6, 7days visit they will have blood drawn, urine and genital tract samples collected for biomarker studies and archiving. At the 6, and pending funding 12 and 18 month visits they will be offered an HIV test by study staff according to national guidelines, and a dried blood spot will be archived.

At 12 to 18 months, participants will be seen at the research site for a final dried blood spot collection and urine pregnancy test. At the end of the study, the last blood spot available will be tested for HIV by PCR. For participants with positive final HIV PCR, the baseline archived blood spots will be tested for HIV to to exclude window period infections at baseline. In the

event of failure to collect or loss of a PCR result, the relevant rapid test result will be used. In the event of discordance between PCR and rapid test results, the PCR result will be used. In the case of a positive PCR after completion of the study, the participant will be notified by the study staff.

Women who are unable to come to the research site for their final visit will have the option of an outreach visit from study personnel to perform HIV testing.

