### 5.8.5 Study Follow-up procedures

All the participating women will be given a study calling card with a 24 hour number to call and be encouraged to report any adverse events experienced to the research team, who have the responsibility to ensure that such adverse events are appropriately managed and details of the event recorded.

In the event of a problem thought by the participant to be related to the contraceptive method, routine assessment, counselling and management will be offered according to the national contraception guidelines. Strategies to manage possible side-effects without method change will be explored. In the event of discontinuation of either method, alternative choices will be offered to participants according to national contraception guidelines.

Participants will be followed at month 6 and month 6, 7days, and pending funding 12 and 18 months. Participants will receive appropriate compensation for their time and costs for in-person visits (R250 for study visits and R100 for contraception-only visits). Every attempt will be made to contact participants who do not return for follow up including repeated calls to participant's and alternative phone numbers, and where possible home visits (provided consented to). At each contact, participants will be asked to confirm their physical address and description of where they live, as well as at least one contact number for a family member or friend that they will inform about the study and are happy to have contacted by the study team. At scheduled and unscheduled visits, the women will receive free routine clinical care and referral as needed. All participants will have access to the national HIV screening and treatment programme and STI treatment through their local clinics. If any incidental health problems are detected, the women will be referred to the relevant health facilities.

---

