#### **5.9 Criteria for discontinuation of a participant**

Participants who decline to remain in the study will be discontinued. Stopping or changing the allocated method will not be a reason for discontinuation, as analysis will be by intention to treat. Pregnancy or HIV sero-conversion will not be a reason for discontinuation, as other outcomes will remain relevant.

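### If follow-up is funded to 12–18 months, deciding HIV status by PCR on the last blood spot may score some treated seroconverters as uninfected

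*Protocol*

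**What the plan says.** Section 5.8.4 of the protocol fixes how HIV status is determined:

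- Specimen: "At the end of the study, the last blood spot available will be tested for HIV by PCR".
- Rapid test as substitute only: in the "event of failure to collect or loss of a PCR result, the relevant rapid test result will be used".
- Conflict: "In the event of discordance between PCR and rapid test results, the PCR result will be used".
- Look-back: "For participants with positive final HIV PCR, the baseline archived blood spots will be tested for HIV". No look-back follows a negative final PCR, and no spot between baseline and the last one is examined.
- Testing during follow-up: at month 6 and, pending funding, at the "12 and 18 month visits they will be offered an HIV test by study staff according to national guidelines", with a spot archived each time.

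Three other provisions bear on this. Section 5.9 keeps seroconverters in follow-up: "Pregnancy or HIV sero-conversion will not be a reason for discontinuation, as other outcomes will remain relevant". Section 5.8.5 gives access to care: "All participants will have access to the national HIV screening and treatment programme and STI treatment through their local clinics". Section 5 sets the duration: "The follow up period will be a minimum of 7 months, and pending funding up to 18 months". The project summary likewise makes the 18-month HIV PCR subject to funding.

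Section 4.2 says the trial is not powered for HIV acquisition. It is measured so that plausible risk ratios can be given and the data added to a Cochrane review.

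**The concern.** The rule lets a late result overwrite an early one. PCR looks for virus or viral nucleic acid. A rapid test, if it is antibody-based as is usual, normally stays positive once a woman has seroconverted. Treatment can therefore make the two disagree in a woman who really is infected, and the protocol resolves that disagreement in favour of the negative PCR. It makes no exception for an earlier confirmed positive.

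The infections exposed to this are those found early enough for treatment to start before the last spot. Section 1 reports that nearly half of injectable users stop within 12 months, so these are also infections more likely to have been acquired on the allocated method. Expected events are few in a trial of this size, so each one lost matters to the HIV estimate. A last-spot rule also gives no infection date, although section 8.2 plans to adjust HIV seroconversion for duration of follow-up.

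**Working it through.** The plan states no figure on this point, so there is none to reproduce. The check is a case trace followed by an illustrative calculation.

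**Case trace**

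1. A woman is rapid-positive at month 6 (or 12) and a spot is archived (5.8.4).
2. She starts treatment through the national programme (access: 5.8.5).
3. She remains in the study (5.9) and gives a later spot at month 12–18, if those visits are funded.
4. Only that last spot goes to PCR. Suppose it is negative because virus is suppressed.
5. PCR and rapid test disagree, so PCR prevails and she is scored uninfected.
6. The final PCR is negative, so no archived spot is opened.

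Reading discordance as applying only to results from one visit does not change the outcome. An antibody test at the last visit would normally still be positive and would be overridden. If no rapid test were done at that visit, the negative PCR would stand alone. Either way the month-6 positive plays no part.

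A woman who does not return after month 6 is not affected in this way: her last spot is the one taken at that visit.

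**Share of seroconversions missed**

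Inputs:
- Final spot at month 18, the longest follow-up (section 5), or at month 12.
- 221 women per arm, the evaluable number in section 5.6, used only to turn shares into counts.
- *f*, the share of infections before the penultimate visit that are treated and PCR-negative on the last spot. The protocol does not give it; assumed 0.10 to 0.90.
- Incidence, not given; assumed 2, 4 or 6 per 100 woman-years.

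With constant incidence, the share of infections arising before month 12 of 18 is 12/18 = 2/3.
- *f* = 0.10: 2/3 × 0.10 = 0.067
- *f* = 0.90: 2/3 × 0.90 = 0.60

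If the last spot is at month 12, infections before month 6 are 6/12 = 1/2 of the total, and the missed share runs from 1/2 × 0.10 = 0.05 to 1/2 × 0.90 = 0.45.

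In counts per arm over 18 months, infections by time *t* (in years) = 221 × (1 − exp(−incidence × *t*)), and missed = *f* × infections by *t* = 1:

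| Incidence per 100 woman-years | Infections by month 18 | Before month 12 | Missed, f = 0.10 | f = 0.25 | f = 0.50 | f = 0.90 |
|---|---|---|---|---|---|---|
| 2 | 6.53 | 4.38 | 0.44 (6.7%) | 1.09 (16.7%) | 2.19 (33.5%) | 3.94 (60.3%) |
| 4 | 12.87 | 8.67 | 0.87 (6.7%) | 2.17 (16.8%) | 4.33 (33.7%) | 7.80 (60.6%) |
| 6 | 19.02 | 12.87 | 1.29 (6.8%) | 3.22 (16.9%) | 6.44 (33.8%) | 11.58 (60.9%) |

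The missed share barely depends on incidence; it is driven by *f*.

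**Effect on the risk ratio**

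Take a true ratio of 1 and incidence 4 per 100 woman-years. The risk by month 18 is 1 − exp(−0.06) = 0.0582, and by month 12 it is 1 − exp(−0.04) = 0.0392.

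- Same *f* in both arms (0.25 or 0.50): ratio 1.0.
- *f* = 0.25 versus 0.50: (0.0582 − 0.25 × 0.0392) / (0.0582 − 0.50 × 0.0392) = 1.25. With the arms reversed, 0.80.

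With equal loss of a share *m* and rare events, the standard error of the log risk ratio grows by about 1/√(1 − *m*): 1.04 at *m* = 0.067, 1.22 at *m* = 1/3, and 1.58 at *m* = 0.60.

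**The case against.** There is a good deal to say on the other side.

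- **The decisive step is not in the protocol.** It names no PCR assay and gives no sensitivity under treatment. The risk is larger with an RNA assay and smaller with a DNA or total nucleic acid assay. Section 5.8.5 gives access to treatment, not uptake. This stands, and it is why the range starts at 10% and why no single figure can be defended. A reader might infer that the rule does delete the early infections, or that at least a third are lost. The documents support neither: the first needs certainty about assay and uptake, the second an unexplained floor of 50% on *f*.
- **Testing is offered, not required.** Not every infection before month 12 will be diagnosed in time for treatment. This stands and pulls the figures down.
- **The later visits are conditional.** One sentence in 5.8.4 describes a final spot at 12 to 18 months without the funding caveat, but it must be read with section 5 and the project summary. At the committed 7-month minimum, the last spot comes from month 6 or shortly after, around the first scheduled study HIV test, so little treatment can precede it. This stands.
- **A reader might infer that the HIV risk ratio is biased.** Loss at a similar rate in both arms leaves a null ratio at about 1. The values 1.25 and 0.80 need different missed shares, and nothing in the protocol gives a reason to expect them.
- **PCR precedence has a proper use.** It resolves false-positive rapid tests and catches early infections that antibody tests miss. This stands, and the fix keeps it.
- **Seroconversion is treated elsewhere as an in-study event** (5.9, 8.2), and an SAP might define the endpoint further. That would help, but 5.8.4 states a working rule rather than leaving the matter open, and nothing in the protocol limits it.

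**Conclusion.** The point holds as a conditional one. If follow-up to 12–18 months is funded, section 5.8.4 as written may count as uninfected a woman with an earlier positive rapid test who is treated and PCR-negative on her last spot. No other provision corrects this.

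The size is uncertain: about 7–60% of seroconversions with an 18-month end and 5–45% with a 12-month end, under constant incidence and an assumed *f* of 10–90%. It is small if the trial stops at 7 months. The consequence is mainly fewer events and a wider interval for an exploratory, unpowered HIV comparison; bias needs unequal loss between arms. The estradiol and BDI-II analyses and the sample size are not touched. It is still worth correcting, because the HIV data are meant for evidence synthesis and the remedy is cheap if made before the end-of-study PCR run.

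**What to change.** Amend section 5.8.4 as follows:

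1. Define HIV acquisition as the first confirmed positive at any follow-up visit.
2. For any positive rapid test, PCR-test the archived spot from that same visit and the baseline spot.
3. Let PCR override a rapid test only for samples from the visit at which the rapid test was first positive.
4. State that a later negative PCR does not overturn an earlier confirmed positive.
5. Use PCR on the last spot to find infections not already detected.

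This removes the loss for infections first found and confirmed at a study visit, and it dates them to a visit. It does not reach a woman diagnosed and suppressed through routine care before her first positive study test.

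The override should not be made to depend on treatment status, because that is not among the follow-up items listed in section 5.8.5 and would need new data collection.

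The cost is a few sentences and PCR on a small number of spots already archived. No extra sampling is needed.
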